## Preparation and Administration of Study Medication

PEGASYS will be supplied to patients in commercial packaging each containing four pre-filled syringes containing 180 µg/ml PEGASYS. Patients should be informed to keep syringes stored refrigerated at 2-8 Celsius out of reach of children.

Copegus will be supplied to patients in commercial packaging each containing 168 tablets of 200 mg Copegus or 56 tablets of 400 mg . Patients should be informed to keep tablets stored at room temperature (15-30 Celsius) out of reach of children. Ribavirin should be administered twice-daily with food.

## Blinding and Randomization

This is an open label study with randomization occurring during the screening period, i.e. 4-12 weeks prior to the initiation of pegylated interferon therapy. During randomization patients will be stratified according to gender, age above or below 40 years, and GUCI < or ≥ 1.0 . Randomization will be computerized and will be performed once all inclusion criteria and none of the inclusion criteria have been fulfilled in the e-CRF.

## Compliance

Patients will be asked to record each PEGASYS injection and Copegus dose in a patient diary. Missed or reduced doses should also be recorded. The patient diary should be returned to study site personnel by the end of the study, and be available for inspection at the end of the study.

Missed or reduced doses should be recorded in CRF.

## Treatment Duration

Regardless of treatment arm, all patients with undetectable HCV RNA at week 4 (RVR) as analyzed by the local lab will receive 24 weeks of combination therapy. Similarly patients not achieving RVR will receive 48 weeks of therapy with the exception of patients having detectable HCV RNA at week 12 but not at week 24 (pEVR) where treatment for 72 weeks may be considered if the patient is willing to extend therapy beyond 48 weeks.

## Stopping Rule

Regardless of treatment arm, all patients achieving ≤ 2 log10 reduction in HCV RNA by week 12 or having detectable HCV RNA at week 24, will discontinue therapy and be considered as “non-responders” not having achieved SVR.

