| TRIAL DESIGN | Multicenter, randomized, open-label, parallel group pilot study.  Randomization to the three treatment arms A, B and C will be stratified by gender, age above or below 40 years, and presence of liver cirrhosis/non-cirrhosis (as evaluated by the Gothenburg University Cirrhosis Index (GUCI) 1.0). | | |
| DISCONTINUATION SCHEME | Treatment will be stopped in patients having a decline of HCV-RNA less than 2-log10 after 12 weeks or detectable HCV-RNA after 24 weeks of study treatment as measured by Roche COBAS AmpliPrep/COBAS TaqMan HCV Test (≤15 IU/mL) | | |
| NUMBER OF SUBJECTS | Total of 105 patients, 35 per treatment group. | | |
| TARGET POPULATION | Men and women >18 years old with CHC genotype 1 will be enrolled in this study. Patients must have quantifiable HCV-RNA, and must have compensated liver disease (Child-Pugh Grade A). Liver biopsies and/or FibroScan evaluations are encouraged especially for patients with a Gothenburg University Cirrhosis Index (GUCI, a cirrhosis index calculated by (normalized AST x PK-INR x 100) / Platelet count (x 109/L)) 1.0, but not mandatory. Patients with other forms of liver disease, human immunodeficiency virus (HIV) infection, hepatocellular carcinoma, anemia, pre-existing severe depression or other psychiatric disease, significant cardiac disease, renal disease, seizure disorders, or severe retinopathy, or previously treated with interferon/ peg-interferon with or without ribavirin are excluded. | | |

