## Secondary Objectives

To prospectively evaluate:

- the efficacy of 2 week loading or 4 week priming followed by concentration targeted dosing of ribavirin in combination with peginterferon alpha-2a in interferon naïve patients with chronic hepatitis C (CHC) virus genotype 1 infection as compared to standard-of-care dosing of ribavirin in combination with peginterferon alpha-2a as evaluated by the proportion of patients achieving VRVR ( “very rapid virologic response” i.e. HCV-RNA below 1000 U/mL at treatment day 7 after intiation of PEG-interferon), RVR (“rapid virologic response”, undetectable HCV-RNA at treatment day 28 after intiation of PEG-interferon), cEVR (“complete early virologic response”, i.e. undetectable HCV-RNA at treatment week 12 after intiation of PEG-interferon), and pEVR (“partial early virologic response”, i.e. decline of HCV-RNA by at least 2 log10 compared with baseline at treatment week 12 after intiation of PEG-interferon).
- the efficacy of 2 week loading or 4 week priming followed by concentration targeted dosing of ribavirin in combination with peginterferon alpha-2a in interferon naïve patients with chronic hepatitis C (CHC) virus genotype 1 infection is superior to standard-of-care dosing of ribavirin, peginterferon alpha-2a therapy as evaluated by sustained virological response (SVR, undetectable HCV-RNA 24 weeks after end of treatment).
- the predictive value of monitoring of viral load at day 0 (before the 1st dose of peginterferon alpha-2a), day 3, day 7 (before the 2nd dose of peginterferon alpha-2a), and day 28 (before the 5th dose of peginterferon alpha-2a) for determining which patients will obtain a sustained virological response (SVR) when treated with ribavirin and peginterferon alpha-2a therapy.
- the association between the trough concentrations of ribavirin (day 1, day 3, day 7, day 28, week 8, week 12, week 16, and end-of-treatment), and the therapeutic efficacy of ribavirin and peginterferon alpha-2a therapy.
- The association between plasma IP-10 (days 0, 1, 3, 7, and 14, and weeks 8, 18, and 24), and the therapeutic efficacy of ribavirin and peginterferon alpha-2a therapy.
- the effect of IL-28B polymorfism on the viral kinetic response and SVR.
- the effect of baseline vitamin D concentrations on the viral kinetic response and SVR.

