# STUDY POPULATION

## Target Population

Men and women ≥ 18 years old with CHC genotype 1 will be enrolled in this study. Patients must have HCV-RNA ≥ 15 IU/mL, and compensated liver disease (Child-Pugh Grade A). Patients with other forms of liver disease, human immunodeficiency virus (HIV) infection, hepatocellular carcinoma, anemia, pre-existing severe depression or other psychiatric disease, significant cardiac disease, renal disease, seizure disorders, or severe retinopathy will not be included.

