### SVR rate defined as percentage of patients with non-detectable HCV-RNA as measured by TaqMan PCR at 24 weeks post completion of the treatment period in the three study arms.

### Relapse rates defined as percentage of patients with non-detectable HCV-RNA as measured by TaqMan PCR at the end-of-treatment but with detectable HCV-RNA 24 weeks post completion of the treatment period in the three study arms.

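### The week-12 stopping rule makes no provision for undetectable HCV-RNA, so a responder with a low baseline can be stopped and labelled non-SVR, in conflict with the measured SVR endpoint and the 24-week duration rule

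*Protocol*

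**What the plan says.** **Entry.** Section 4.1: "Patients must have HCV-RNA ≥ 15 IU/mL, and compensated liver disease (Child-Pugh Grade A". The Synopsis (Target Population) puts it as "Patients must have quantifiable HCV-RNA". Neither place sets a higher floor. The Synopsis Discontinuation Scheme gives the same 15 IU/mL as the figure for the assay.

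**Week-12 rule.** The Stopping Rule in Section 7.5 covers "all patients achieving ≤ 2 log10 reduction in HCV RNA by week 12", in every arm. Those patients, and patients detectable at week 24, leave therapy and are classed as non-responders without SVR. The Synopsis (Safety) and Section 5.3.2 repeat the stop at 2 log10 or less. The Synopsis Discontinuation Scheme draws the line differently: "Treatment will be stopped in patients having a decline of HCV-RNA less than 2-log10 after 12 weeks". None of these texts mentions a patient who is undetectable at week 12.

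**Duration.** Section 7.5, Treatment Duration, also for every arm: "all patients with undetectable HCV RNA at week 4 (RVR) as analyzed by the local lab will receive 24 weeks of combination therapy".

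**SVR.** Section 9.1.2: "SVR rate defined as percentage of patients with non-detectable HCV-RNA as measured by TaqMan PCR at 24 weeks post completion". Section 6.2 agrees. Neither attaches a week-12 condition.

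**Other response terms.** Section 2.2 defines cEVR as undetectable at week 12, pEVR as a fall of 2 log10 or more at week 12, and VRVR by an absolute level: "i.e. HCV-RNA below 1000 U/mL at treatment day 7 after intiation of PEG-interferon".

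**Background.** Section 1.4.2 describes week-12 response in a cited trial as either a 2-log fall or an undetectable result.

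**The concern.** The stopping rule is written purely as a size of fall, and the size of fall that can be shown depends on where the patient starts. With entry open down to the assay figure, some eligible patients may have no room to show more than 2 log10 even if the virus disappears. The background description of week-12 response has a second branch for undetectable HCV-RNA, and the rule does not carry it over.

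Two things are at stake. Sites receive instructions that cannot both be followed for the same patient: 24 weeks because of RVR, and a stop at week 12. Analysts receive two ways to score SVR: the follow-up measurement, or a label fixed at week 12. The affected patients have cleared virus early, so scoring them as failures by rule would turn apparent successes into failures.

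A lesser matter is VRVR. A patient who enters below 1000 IU/mL and does not change meets it at day 7.

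**Working it through.** There is no stated figure to reproduce. The check is threshold arithmetic on the protocol's own cut-offs.

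**Inputs.** Entry floor 15 IU/mL (Section 4.1); assay figure 15 IU/mL (Synopsis, Discontinuation Scheme); stop if the fall is 2 log10 or less (Section 7.5); VRVR cut 1000 U/mL (Section 2.2); 35 patients per arm, 105 in all (Section 3.2). The value assigned to an undetectable result, *u*, is not stated, so I take 15, 7.5 and 1 IU/mL as assumptions.

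**Step 1: largest measurable fall** = log10(baseline / *u*).

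| Baseline (IU/mL) | *u* = 15 | *u* = 7.5 | *u* = 1 |
| --- | --- | --- | --- |
| 15 | 0.00 | 0.30 | 1.18 |
| 100 | 0.82 | 1.12 | 2.00 |
| 750 | 1.70 | 2.00 | 2.88 |
| 1000 | 1.82 | 2.12 | 3.00 |
| 1500 | 2.00 | 2.30 | 3.18 |

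An undetectable patient meets the rule when the baseline is at most 100 × *u*: 1500, 750 or 100 IU/mL. Some eligible range is caught under each convention.

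**Step 2: follow one patient.** Baseline 1000 IU/mL, undetectable at day 28 and week 12, *u* = 15.

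- Section 2.2: RVR and cEVR.
- Treatment Duration: 24 weeks of combination therapy.
- Stopping Rule: fall log10(1000/15) = 1.82, so therapy ends at week 12 and the patient is labelled non-SVR.
- Sections 6.2 and 9.1.2: SVR if undetectable 24 weeks after treatment.
- Section 5.3.1 expects early discontinuers to return for that sample. Section 8.4 expects it of those who stop after the first 12 weeks with an undetectable last result.

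The follow-up result is therefore meant to be collected, and the label can contradict it.

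**Step 3: how many patients.** The protocol gives no baseline distribution. Assume log10 baseline is normal. With log10(1500) = 3.176 and log10(1000) = 3:

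| Assumed mean, SD | P(≤1500) × 105 | P(<1000) × 105 |
| --- | --- | --- |
| 6.0, 0.8 | 0.00021 × 105 = 0.02 | 0.00009 × 105 = 0.01 |
| 5.5, 1.0 | 0.01007 × 105 = 1.1 | 0.00621 × 105 = 0.65 |
| 5.0, 1.0 | 0.03408 × 105 = 3.6 | 0.02275 × 105 = 2.4 |

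The middle column uses the widest range (*u* = 15); the other conventions give fewer. One patient moves an arm's rate by 1/35 = 2.9 percentage points.

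**Step 4: the boundary.** A fall of exactly 2 log10 continues under the Synopsis Discontinuation Scheme, stops under Sections 5.3.2 and 7.5, and counts as pEVR under Section 2.2.

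**Step 5: VRVR.** An unchanged patient at 15 to 999 IU/mL is below 1000 at day 7. No baseline or decline condition applies.

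**The case against.** Several points on the other side are sound.

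- **Precedence.** A reader might infer that these patients are definitely scored as SVR failures. The protocol does not say so: nothing ranks the Stopping Rule above Sections 6.2 and 9.1.2, and early stoppers are called back for sampling. It is an unresolved conflict, not a fixed failure score.
- **Undetectable is censored.** A reader might infer that nobody at or below 1500 IU/mL can ever show a 2 log10 fall. That holds only with undetectable set to 15. Substitution is commonly left to an analysis plan, and under the other values tried the range shrinks to 750 or 100. It does not vanish.
- **Numbers.** The expected count may be close to zero. A material bias in the arm comparison cannot be claimed.
- **Exact boundary.** On a continuous log scale a fall of exactly 2 log10 is nearly an empty case. The wordings still differ, but few patients, if any, will turn on it.
- **The non-SVR label has a use.** It gives true week-12 non-responders a stated outcome. Deleting it would leave those without a follow-up sample unscored.
- **VRVR.** Any absolute threshold depends on baseline, VRVR is one of many secondary variables, and the primary endpoint already measures decline. A reader might want to restrict its denominator by day 0 HCV-RNA. That would be unsound: in Group B, day 0 follows four weeks of randomised ribavirin, so the restriction would condition on a post-randomisation value in one arm only.

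None of this removes the collision between the Stopping Rule and Treatment Duration, or the two routes to an SVR score. The Section 1.4.2 description concerns a cited trial and does not amend the rule, but it is the nearest text in the protocol for a reconciliation.

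**Conclusion.** The point holds as a conflict of definitions, probably with a small numerical effect. As written, a patient with a low baseline who is undetectable at weeks 4 and 12 falls under two incompatible treatment instructions and two incompatible SVR scores. This needs only the stated entry floor, the rule's wording and any of the three conventions tried for an undetectable result.

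The size rests on assumptions: an affected baseline of up to 1500, 750 or 100 IU/mL depending on that convention, and about 0 to 4 of 105 patients under the assumed distributions. The documents do not support a claim that trial results would be materially distorted, or that VRVR is invalid as an endpoint. The conflict is still worth correcting because it is cheap to do so and each affected patient is worth 2.9 percentage points in an arm of 35.

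**What to change.** 1. Score SVR in every arm from the HCV-RNA result 24 weeks after treatment, as Section 9.1.2 defines it.
2. Keep the non-SVR label in the Stopping Rule but limit its reach. It should not override an observed undetectable follow-up result; it should remain for patients who are detectable or have no follow-up sample.
3. The sponsor should reconcile the Synopsis (Discontinuation Scheme and Safety), the pEVR definition in Section 2.2, Section 5.3.2, and both Treatment Duration and Stopping Rule in Section 7.5, so that they give one instruction at the 2 log10 boundary and one for patients undetectable at week 12. Which clinical rule applies is for the sponsor to decide.
4. Keep VRVR on all dosed patients. At most, add a sensitivity analysis restricted by the screening HCV-RNA, which is taken before treatment in all arms, and not by day 0.

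The cost is protocol wording. Section 5.3.1 already expects the follow-up sample from early discontinuers, so no new visit or assay is needed. The optional sensitivity analysis would drop the few patients who enter with low viral load.

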# SAFETY ISSUES

## Adverse Events and Laboratory Abnormalities

### Clinical Adverse Events

An Adverse Event (AE) is any untoward medical occurrence in a patient or clinical investigation subject administered a pharmaceutical product and which does not necessarily have to have a causal relationship with this treatment. An AE can therefore be any unfavorable and unintended sign (including an abnormal laboratory finding, for example), symptom, or disease temporally associated with the use of a medicinal product, whether or not considered related to the medicinal product. Pre-existing conditions, which worsen during a study are to be reported as AE.

All clinical adverse events (AEs) encountered during the clinical study will be reported on the AE page of the CRF. Intensity of adverse events will be graded on a four‑point scale (mild, moderate, severe, life‑threatening) and reported in detail as indicated on the CRF. Relationship of the adverse event to the treatment should also be assessed.

**Flu-like symptoms**

The following events can be reported as flu-like symptoms: Fatigue, headache, pyrexia, myalgia and rigors

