- the association between liver histology as evaluated by the Ishak scoring system (modified HAI score) and steatosis grading, and the therapeutic efficacy of peginterferon alfa-2 combination therapy with ribavirin.
- the association between liver stiffness as evaluated by the FibroScan and the therapeutic efficacy of peginterferon alfa-2 combination therapy with ribavirin.
- the association between liver fibrosis as evaluated by the GUCI and APRI indexes as well as hyaluronic acid, and the therapeutic efficacy of peginterferon alfa-2 combination therapy with ribavirin.
- the association between body mass index (BMI), waist circumference, weight and age, and the therapeutic efficacy of peginterferon alfa-2 combination therapy with ribavirin.
- the predictive value of monitoring CD56 negative NK, CD4+ CD38+, CD8+ CD38+, CD8+CD16+, Foxp3+, and pDC (CD303+) cells in peripheral blood and liver biopsies as analyzed by FACS prior to and after the initiation of therapy for determining which patients will obtain a sustained virological response (SVR) when treated with peginterferon alfa-2 and ribavirin combination therapy.
- the predictive value of quantifying mRNA expression in pre-treatment liver biopsies for IFI-27, IP-10, CXXL-6, IL-2, IL-8, IL-10, -IFN, TNF-, KRT19, COL1A1, MMP7, TIMP1, FASL, AIF1 for determining which patients will obtain a sustained virological response (SVR) when treated with peginterferon alfa-2 and ribavirin combination therapy.

Others:

To prospectively evaluate:

- the predictive value of monitoring the trough concentrations of ribavirin (day 1, day 3, day 7), and the final steady-state concentration of ribavirin.
- the safety of peginterferon alpha-2a combination therapy with concentration targeted dosing of ribavirin in combination peginterferon alpha-2a, based on accumulated number of adverse events and severe adverse events as well as the impact on quality of life during treatment and follow-up phase.
- the safety of peginterferon alpha-2a combination therapy with concentration targeted dosing of ribavirin in combination peginterferon alpha-2a, with particular regards to the number of patients in each treatment arm developing anemia grade 1 (10.5-9.5 g/dL), grade 2 (9.4-8.0 g/dL), grade 3 (7.9-6.5 g/dL), and grade 4 (<6.5 g/dL).

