# STUDY design

## Overview of Study Design and Dosing Regimen

This study will be conducted as a phase III, open label, multicenter trial. A total of 105 patients will be randomized to one of three possible treatment groups.

**Group A:** (“Loading”): PEG-IFN α-2a 180 g/week plus loading (≥26 mg/kg/day for 2 weeks followed by ≥13 mg/kg/day) and concentration targeted (≥ 2.5 mg/L (10.25 μmol/L) 28 days after initiation of ribavirin therapy) dosing of ribavirin and response guided treatment duration (RVR 24 weeks, non-RVR 48 weeks, pEVR consider 72 weeks), follow-up period 24 weeks.

**Group B**: (“Priming”): Standard-of-care dosing of ribavirin (≥13 mg/kg/day) without PEG-IFN for 4 weeks followed by 24-48 additional weeks of PEG-IFN α-2a 180 g/week plus standard-of-care dosing of ribavirin (≥13 mg/kg/day) and concentration targeted (≥ 2.5 mg/L (10.25 μmol/L) 28 days after initiation of ribavirin therapy) dosing of ribavirin and response guided treatment duration (RVR 28 weeks, non-RVR 52 weeks, pEVR consider 76 weeks), follow-up period 24 weeks.

**Group C:** (“Standard-of-Care”): PEG-IFN α-2a 180 g/week plus standard-of-care dosing of ribavirin (≥13 mg/kg/day without any measurement of ribavirin concentration) and response guided treatment duration (RVR 24 weeks, non-RVR 48 weeks, pEVR consider 72 weeks), follow-up period 24 weeks.

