### SVR rate and percentage of patients with normal serum ALT levels at 24 weeks after completion of the treatment period in the total patient population, and its association with the following factors:

### early virological response

### pharmacokinetic response to ribavirin

### Secondary Safety Variables

- Adverse event rate and profile
- Other laboratory tests
- The proportion of patients experiencing anemia grade 1 (10.5-9.5 g/dL), grade 2 (9.4-8.0 g/dL), grade 3 (7.9-6.5 g/dL), and grade 4 (< 6.5 g/dL) will be evaluated in each study arm.

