#### Safety Data Analysis

Adverse events will be assigned preferred terms and categorized into body systems according to the Medical Dictionary for Drug Regulatory Affairs (MedDRA) classification of the World Health Organization (WHO) terminology. In the analyses adverse events occurring during treatment and within 168 days of last trial medication will be summarized.

The proportion of patients with reported adverse events during the target period, will be calculated by dividing the number of these patients by the number of patients that can be evaluated for safety. Adverse events will be summarized by study groups mentioned in Section 9.2.2.1, by body system and event within each body system.

Certain potentially clinically relevant laboratory abnormalities will be analyzed in more detail. These laboratory abnormalities include anemia, neutropenia, thrombocytopenia, and elevated ALT levels.

For hemoglobin, neutrophil and platelet counts the lowest value for each patient during treatment and follow-up will be summarized.

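### The protocol lets reporters enter five symptoms singly or as one flu-like event, so adverse event counts and per-symptom incidences depend on recording habit (minor)

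*Protocol*

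**What the plan says.** The recording rule stands under the Flu-like symptoms subheading of section 8.1.1 (Clinical Adverse Events): "The following events can be reported as flu-like symptoms: Fatigue, headache, pyrexia, myalgia and rigors". It sets no minimum number of symptoms and no default. It does not say whether a symptom already entered by itself may also be grouped.

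The general rule in the same section is "All clinical adverse events (AEs) encountered during the clinical study will be reported on the AE page of the CRF", so single entry of each symptom also complies. Sections 8.1.1 and 8.2.1 have intensity and relationship to treatment assessed for each event.

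These data feed three planned outputs:

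- Section 2.2, under Others, and the synopsis: a safety objective "based on accumulated number of adverse events and severe adverse events".
- Section 9.1.3: the safety variable "Adverse event rate and profile".
- Section 9.2.1.3: a patient-level proportion ("The proportion of patients with reported adverse events during the target period, will be calculated by dividing the number of these patients") and a summary by arm "by body system and event within each body system".

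On blinding, section 3.1 says: "This study will be conducted as a phase III, open label, multicenter trial".

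**The concern.** Two reporters who both follow the protocol can turn the same clinical episode into different numbers of records. An output that counts events, or that gives the incidence of a named symptom, then partly measures recording style. Centers in four countries may well differ in habit. Because the reporter knows the arm, habit may also differ between arms.

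The loss runs one way. Single entries can be pooled into a flu-like group at any later stage, but a grouped entry does not show in the CRF data which of the five symptoms were present. It also holds one intensity grade and one relationship assessment for up to five symptoms, and the protocol does not say which symptom's grade applies, so the count of severe events is touched as well. An analysis plan cannot repair this afterwards, so the rule has to be settled at data collection.

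At stake is the descriptive comparison of tolerability between arms, in a pilot trial that names safety among its aims (sections 9.2.1 and 9.3).

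**Working it through.** The protocol gives no figure on this point, so there is none to reproduce.

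**Step 1: counting from the text alone.** Let k be the number of listed symptoms in one episode (k = 1 to 5).

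- Grouped: 1 record.
- Entered singly: k records.

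As an extreme illustration, suppose all 35 patients of an arm (section 3.2) have one episode with all five symptoms.

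| Output | Always grouped | Always single |
|---|---|---|
| Records | 35 × 1 = 35 | 35 × 5 = 175 |
| Patients with headache recorded | 0/35 | 35/35 |
| Patients with any adverse event | 35/35 | 35/35 |

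The event count and the symptom incidence move with the convention. The proportion of patients with any adverse event does not.

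**Step 2: a less extreme case, on assumed inputs.** The protocol gives no symptom rates. Assume, for illustration only, fatigue 50%, headache 45%, pyrexia 40%, myalgia 35% and rigors 25%, occurring independently, with the same rates in every arm.

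- Mean records per patient, all single: 0.50 + 0.45 + 0.40 + 0.35 + 0.25 = 1.95.
- Mean records per patient, all grouped: 1 − (0.50 × 0.55 × 0.60 × 0.65 × 0.75) = 1 − 0.080 = 0.92.
- Relative difference: (1.95 − 0.92)/1.95 = 53% fewer records for the same patients.

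**Step 3: what unequal habits would do between arms.** Let f be the share of patients whose symptoms are grouped, also assumed. The mean count in an arm is (1 − f) × 1.95 + f × 0.92. Fatigue recorded under its own name is 0.50 × (1 − f).

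- f = 0.3: 0.7 × 1.95 + 0.3 × 0.92 = 1.64 records; fatigue 35%.
- f = 0.4: 0.6 × 1.95 + 0.4 × 0.92 = 1.54 records; fatigue 30%.
- f = 0.6: 0.4 × 1.95 + 0.6 × 0.92 = 1.33 records; fatigue 20%.

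| Grouped share, A vs C | Count ratio A:C | Recorded fatigue, A vs C |
|---|---|---|
| Equal | 1.00 | equal |
| 40% vs 60% | 1.54/1.33, about 1.15 | 30% vs 20% |
| 30% vs 60% | 1.64/1.33 = 1.23 | 35% vs 20% |
| 60% vs 30% | 1.33/1.64 = 0.81 | 20% vs 35% |

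No row contains a true difference between arms. With equal shares the ratio stays at 1.00, although both counts and both symptom incidences are still understated relative to single entry.

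**The case against.** The strongest defence is that the reach is small. The accumulated event count appears only under Others, below the primary and secondary objectives, and no test or sample size rests on it. The one adverse event measure that section 9.2.1.3 defines by formula is a proportion of patients, and its overall value does not change. Grouping expected symptoms also fits the protocol's other economies in recording, such as the thresholds in section 8.1.2 and the paracetamol and ibuprofen exemptions in section 4.4. The CRF and its instructions, which are not shown, might complete the rule. All of this stands as a limit on the size of the problem. It does not remove the problem, because the stated rule itself allows records that cannot be compared.

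Three stronger readings are tempting, and the protocol does not support them.

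- *Grouping hides a ribavirin effect, since fatigue can accompany anemia.* Section 8.5.2.3 names anemia as the primary toxicity, but graded anemia by arm is a safety variable of its own (section 9.1.3) and the lowest hemoglobin per patient is summarized (section 9.2.1.3). Grouping can blur the incidence of fatigue. It does not conceal the anemia result.
- *The counts are biased against Groups A and B.* One could argue that knowledge of the arm, or Group B's four weeks without interferon, leads to more single entries there. Nothing in the protocol shows this. All arms receive the same peginterferon dose, and equal or reversed habits are just as possible.
- *Any patient may score 1 to 5, with the detail lost for good.* The range is 1 to k. Source notes kept under section 16.1 may allow some recovery, though laboriously.

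**Conclusion.** The point holds as a minor flaw in data collection. Following the protocol as written, an episode with k listed symptoms yields 1 or k records. The accumulated number of adverse events and the event-level incidences therefore depend on recording habit, which may vary by site and, in an open-label trial, by arm in either direction.

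The 1-or-k result rests on the text alone. The 53% difference and the ratios from 0.81 to 1.23 rest on assumed symptom rates, independence and assumed grouping shares. They show what could happen and are not estimates for this trial. The overall proportion of patients with an adverse event, the graded anemia analysis and the primary virological endpoint stand as planned.

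**What to change.** Replace the permissive sentence under Flu-like symptoms in section 8.1.1 with one mandatory convention: each of the five symptoms is recorded on the adverse event page under its own term, with its own intensity and relationship. Align the CRF instructions with it.

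If a flu-like group is wanted, derive it in the analysis from the protocol's own five-symptom list by a prespecified definition, for example a minimum number of concurrent symptoms. Such a minimum keeps an isolated headache from being labelled flu-like, and using the full list keeps fatigue in the group. Count the group once per patient and report each component by arm alongside it.

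The cost is one protocol sentence, matching CRF guidance and a few more adverse event lines per patient. No treatment rule changes.
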